## Abstract

**Background:**

As the demand for nursing home (NH) services increases, older adults and their families expect exceptional services. Neighbourhood Team Development (NTD) is a multi-component intervention designed to train team members (staff) in the implementation of resident-centered care in NH settings. A neighbourhood is a 32-resident home area within a NH. This paper presents the protocol used to implement and evaluate NTD. The evaluation aimed to 1) examine fidelity with which the NTD was implemented across NHs; 2) explore contextual factors associated with implementation and outcomes of the NTD; and 3) examine effects of NTD on residents, team members, family, and organizational outcomes, and the association between level of implementation fidelity and outcomes.

**Methods:**

The study employed a repeated measure, mixed method design. NTD consisted of a 30-month standardised training and implementation plan to modify the physical environment, organize delivery and services and align staff members to promote inter-professional team collaboration and enhanced resident centeredness. Training was centred in each 32-resident neighbourhood or home area. Quantitative and qualitative data were collected with reliable and valid measures over the course of 3 years from residents (clinical outcomes, quality of life, satisfaction with care, perception of person centeredness, opportunities for social engagement), families (satisfaction with care for relative, person centeredness, relationship opportunities), team members (satisfaction with job, ability to provide person centered care, team relationships) and organizations (retention, turnover, staffing, events) in 6 NHs. Mixed models were used for the analysis.

**Discussion:**

The advantages and limitations of the NTD intervention are described. The challenges in implementing and evaluating this multi-component intervention are discussed as related to the complexity of the NH environment.

**Trial registration:**

ClinicalTrials.gov ID: NCT03415217 (January 30, 2018 – Retrospectively registered).

## Contribution to the literature

Older adults and their families expect exceptional services and care in nursing homes.Neighbourhood Team Development (NTD) is an approach that focuses on resident-centred care in nursing homes.This manuscript explores the advantages and limitations of implementing NTD, and discusses evaluation strategies to look at the fidelity of the approach and its effects on residents, team members, family and the overall organization.These findings contribute to the important topic of how to implement, evaluate and sustain a resident-centred model of care in nursing homes.

## Background

Population ageing is a significant global demographic trend, which will continue to increase [1]. In 1950, the number of older persons was 202 million across the world. From 1950 to 2013, this population increased four-fold, and is expected to triple by 2050 [2]. The number of older persons living with complex co-morbidities and dementia worldwide is approximately 47.5 million, with a projected increase to 75.6 million by 2030, and more than triple by 2050 [1]. Older adults with dementia often move to residential environments, such as nursing homes (NHs) to receive 24-h care to address their needs [3].

Older people residing in NHs and their families expect excellent care and services from the care team. However, literature and anecdotal evidence indicate that the quality of care in NHs is not necessarily resident and family centred, and that staff do not always collaborate as a team in providing appropriate and tailored care; instead they are task focused and work in silos, which may compromise the residents’ quality of life [4, 5]. Two main barriers that limit the ability of a care team to support residents’ care and quality of life are a) the traditional organizational NH design that does not account for resident centeredness and b) major skills misalignment so staff function independently as opposed to working as a team.

This paper describes the study protocol for implementing and evaluating *Neighbourhood Team Development* (NTD), a multi-component, organizational intervention to enhance team development and resident centeredness in NHs. The NTD training program was informed by the work of Eden Alternative, and was originally developed by Vivage Quality Health Partners**©** [6] and others [7, 8] examining care teams and resident centeredness in NHs. In 2010, the Eden Alternative designed a training course for Neighbourhood Guides, staff in NHs who are to support and mentor teams to implement resident-centred care at the “neighbourhood” level (a limited number of rooms and living space within the larger NH). Although the course offered a strong foundation in team development, it lacked clearly defined integration of resident centred practices, was not aligned with the organizational context in which neighbourhoods were to be implemented in the organization interested in adopting the program, and did not provide guidance on how the program implementation should be evaluated.

Schlegel Villages, a large group of private retirement and NHs in Ontario, Canada, and the investigators used this course (with permission) as a starting point to develop an integrated change program, NTD, that extends the training of individual neighbourhood guides within a large organizational change process. NTD was implemented over a three-year period, involving standardised training followed by care team training (per neighbourhood).

NTD consists of three components: 1. Modifying the physical NH environment, 2. Reorganizing the organization and delivery of care and services, and 3. Aligning team members to collaborate in providing resident-centred care. In addition, NTD intentionally includes strategies to address traditional organizational design and skills misalignment. This focus makes NTD unique in that no other resident centred programs have integrated these elements. Core beliefs of NTD include consistent team assignments to a dedicated neighbourhood, respect of residents’ choice and autonomy, and self-directed work teams on each neighbourhood (Table 1).

**Table 1 Tab1:** Core Beliefs of NTD

Core Belief	Description
Consistent team assignments to dedicated neighbourhood	• Redesign of organizational structure to move from siloed departments and hierarchical management to cross-functional teams. • Empowering cross-functional neighbourhood teams to be more effective and responsive to resident-centred decision-making. • Cross-training and blending of roles to allow for greater flexibility and cohesiveness of care by eliminating task orientation and job delineation.
Respect for residents’ choice and autonomy	• Redesign of NH services to fit needs and expectations of residents with complex needs. • Redesign of physical environment to promote resident-centeredness.
Self-directed work teams per neighbourhood	• Financial framework of accountability by emphasizing team members working to full scope of practice while providing better coordinated care. • Solidified approach to seamless team functioning where residents come first.

There is a steadfast growth in NHs adopting resident centred practices. To be resident-centred is to have a home as an environment that directs and supports close relationships among team members, residents and their families, residents’ choices and team member empowerment and collaborative decision making, with the goal of improving quality processes.

Public pressure on NHs and the potential for decreased care quality for complex residents within a traditional design encourages NH leaders and practitioners to start changing their care models. Given this trend, there is a real need to identify effective resident-centred care models and build evidence informed implementation and evaluation plans. The complexity of care in NHs calls for a multi-pronged approach to implementation and evaluation and is likely the reason why several narrowly focused interventions were neither successful nor sustainable.

Researchers, professionals and policy makers agree that the quality of care delivered in NHs is often inconsistent and generally suboptimal. Empirical evidence [3] demonstrates several interconnected concerns including increased resident care needs, low staff-resident ratios and limited team work [8], regulatory standards that are inconsistent with resident-centred care [9], resident and family dissatisfaction [10], staff burnout and low retention [11, 12], over- regulation, [13], lack of innovative leadership [14], and concerns about current and future capacity to respond to the needs of those with ADRD [15].

Overall, a review of studies that evaluated resident centred care models showed promising results related to the residents’ quality of life and resident-centred care. Yet, findings for team members, family and organizations are limited, with at times mixed results on satisfaction and turnover data. This might be due to the limited understanding and implementation of resident-centred interventions. There remains little data on sustainability of programs, as well as effectiveness of program components.

### Aims

The goal of this current study was to implement and evaluate NTD. The specific objectives were to: 1. Examine the fidelity of the program when implemented in a multi-home NH organization; 2. Explore contextual factors associated with implementation and outcomes; 3. Examine the effects of the program on residents, team members, family, and organizational outcomes and the association between the level of implementation fidelity and outcomes, and; 4. Determine the mechanisms through which NTD exerts its effects.

## Methods

### Design

A multi-component intervention for a single group was used. NTD involved a 30-month implementation plan, starting with a 3-day training for all management and neighbourhood coordinators (NCs), team leaders who are trained to coordinate care service and delivery for two specific neighbourhoods and is the designated primary contact for residents and their family members, followed by individual team development on all neighbourhoods across the home for 12 months. Upon the start of the 2nd implementation year, the second training session for management and NCs took place (3-day training), again followed by a 12-month implementation plan on the neighbourhoods. A third and last training with management and NCs took place at the start of the third implementation year, followed by a 6-month implementation.

Training for management and NCs was delivered by NTD experts over the course of two consecutive days, twice per year, followed a training manual, and included competencies in care coordination, care and service delivery for the neighbourhoods, team’s interpersonal skills and care competencies, care decision support based on group processes, awareness and knowledge to promote residents’ choices, and skills for ongoing supervision and stewardship of the team. Individual team development per neighbourhood was delivered by the NCs on a quarterly base (4 h per session) and consisted of interactive group modules building capacity in team attributes, professional competencies relating to knowledge and skills to support resident centeredness (i.e., resident-centred decision making, reprioritizing care consistent with the residents’ preferences) and competencies in relational care and in the delivery of care and services. The researchers adhered to the Standard Protocol Items: Recommendations for Interventional Trials (SPIRIT) guidelines.

### Sample and recruitment

This study aimed for a rigorous evaluation of the process and complex outcomes of NTD implementation and used a pragmatic real-world effectiveness approach; as such, no formal eligibility criteria or sample size calculations were completed. Data were available from 11 LTC homes, serving 192 residents, which is approximately 2112 residents in total. The number of team members providing direct care varied over time and by LTC home. The sample for the study included residents (*n* = 1110), family members (*n* = 62) and team members (*N* = 2173) of 11 NHs in Ontario, Canada. Given data availability, the power of this study to detect an increase in residents’ self-reported quality of life was based on a one-sample t-test. Assuming an effect size of 0.2, standard deviation of 10, and sample size of 2112, the study will have a power of 0.81 to test change over time. Sample size calculations were performed using SAS University Edition (SAS Institute Inc., North Carolina, USA).

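### The stated power of 0.81 does not follow from effect 0.2, SD 10 and n = 2112 under any reading of the effect size

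*Protocol article*

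**What the plan says.** The power statement is in the protocol article, Methods, under Sample and recruitment. The test is named there: "the power of this study to detect an increase in residents’ self-reported quality of life was based on a one-sample t-test". The result follows: "Assuming an effect size of 0.2, standard deviation of 10, and sample size of 2112, the study will have a power of 0.81". The 2112 is the capacity of the homes: "Data were available from 11 LTC homes, serving 192 residents, which is approximately 2112 residents in total". The same paragraph gives the residents in the study sample as 1110.

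The article does not say whether 0.2 is in scale points or SD units, or whether the SD of 10 refers to scores or to change. With the power figure it states no alpha, sidedness, intraclass correlation (ICC), design effect or baseline-to-follow-up correlation.

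The paragraph also says that "no formal eligibility criteria or sample size calculations were completed", and it ends with "Sample size calculations were performed using SAS University Edition".

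**The concern.** The article names a test, an effect, an SD, a sample size and a power. Given a conventional alpha, the first four determine the fifth, so the statement can be checked. It fails the check, and the two possible readings of 0.2 miss 0.81 in opposite directions.

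This is the only figure offered to support the study's ability to detect an improvement in residents' quality of life. On the raw reading, a null result would say almost nothing about a 0.2-point change. On the standardised reading, changes much smaller than 0.2 SD would reach significance. A reader who takes 0.81 at face value would believe neither of these.

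**Working it through.** **Inputs from Sample and recruitment:** one-sample t-test; effect 0.2; SD 10; n = 2112; stated power 0.81. **Assumption:** alpha 0.05, with both one- and two-sided tests tried, because neither is stated and the word increase could suggest one-sided.

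**Formula.** Noncentrality = (effect / SD) × √n. Power is the probability that a noncentral t with n − 1 degrees of freedom exceeds the critical value. √2112 = 45.96.

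**Attempt to reproduce 0.81**

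| Reading of 0.2 | Noncentrality | Two-sided 5% | One-sided 5% |
|---|---|---|---|
| Raw, SD 10 (d = 0.02) | 0.02 × 45.96 = 0.919 | 0.151 | 0.234 |
| Standardised (d = 0.2) | 0.2 × 45.96 = 9.19 | > 0.9999 | > 0.9999 |

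Changing alpha does not help: from 0.01 two-sided to 0.10 one-sided, the raw reading runs from 0.049 to about 0.36. With the 1110 residents in the study sample, the raw reading gives 0.102 two-sided (0.164 one-sided) and the standardised reading stays above 0.9999.

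**What 0.81 would require (two-sided 5%; normal approximation with z = 1.960 and 0.878, sum 2.838)**

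- Effect at n = 2112: 2.838 / 45.96 = 0.0618 SD, or 0.62 points with SD 10 (0.55 points one-sided).
- n for a raw change of 0.2 with SD 10: (2.838 / 0.02)² ≈ 20,100.
- n for a standardised effect of 0.2: (2.838 / 0.2)² ≈ 201. The exact t gives 0.8095 at n = 203.

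**Unstated inputs that would bring the figure near 0.81**

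- *Clustering by home with d = 0.2.* 2112 / 203 = 10.4, so a design effect of about that size is needed. An assumed ICC of 0.05 with 192 residents per home gives 1 + 191 × 0.05 = 10.55. The effective n is then 2112 / 10.55 = 200, and power is 0.804 by exact t (0.808 by normal approximation).
- *SD of 10 refers to scores, raw change 0.2.* The SD of change would be 10 × √(2(1 − r)). Power of 0.81 needs r of about 0.95 two-sided or 0.93 one-sided.
- *10 is a variance, raw change 0.2.* SD = √10 = 3.16 gives power 0.828, close to the stated figure but not equal to it.

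None of these inputs appears in the article.

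**The case against.** The strongest defence is that the arithmetic may be sound and only the reporting incomplete. A condensed article can leave an ICC or a correlation to a fuller document, and a standardised 0.2 with an ICC near 0.05 by home comes close to 0.81. This stands as a caution about cause: the article does not show whether the fault is a slip, a mislabelled input or an omitted adjustment. It does not rescue the sentence. The article describes a plain one-sample t-test on 2112 residents, and the figures it prints for that test are incompatible. If clustering was allowed for, the calculation is misdescribed.

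The second defence is that the two remarks about sample size calculations can be reconciled: the study was not sized in advance, and power was then worked out for the data available. That is a fair reading. The fault there is loose wording, and the disclosure that n was not chosen by calculation is worth keeping.

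The third is that little depends on the figure. Numbers were set by data availability, collection ended in March 2017, and results will be read from mixed-model estimates. It is true that no effect estimate changes. The article still makes a quantitative claim about sensitivity that is wrong as written, and it says that analysis is ongoing, so a correction can still inform interpretation.

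**Conclusion.** The concern holds. From the stated inputs, power is about 0.15 two-sided or 0.23 one-sided if 0.2 is a raw change, and above 0.9999 if it is standardised. Neither is near 0.81, and no conventional choice of alpha or sidedness closes the gap. The recomputation assumes alpha 0.05, independent residents (as a one-sample t-test does) and an SD of 10 that applies to the quantity tested. The cause cannot be determined from the article. The paired remarks on sample size calculations are a secondary point of wording. Because this is the study's only power figure, it should be corrected.

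**What to change.** Replace the power sentence with one that states the scale of the effect, whether the SD is of scores or of change, alpha, sidedness, the number of residents analysed (1110 or 2112, with the reason) and the design effect. If an ICC or a correlation was used to reach 0.81, report it. Keep the disclosure that the study was not sized in advance, and change the closing software sentence to refer to a power calculation.

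Since the sample is fixed, a detectable-change statement would serve readers better than a power figure. As an illustration only, take SD 10 as the SD of change, 1110 residents in 11 homes (about 101 per home), 80% power and two-sided 5%:

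- independent residents: 10 × 2.80 / √1110 ≈ 0.8 points;
- assumed home-level ICC 0.02: effective n = 1110 / 3.00 = 370, and 10 × (2.228 + 0.879) / √370 ≈ 1.6 points;
- assumed home-level ICC 0.05: effective n = 1110 / 6.00 = 185, and 10 × (2.228 + 0.879) / √185 ≈ 2.3 points.

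The last two use t quantiles on 10 degrees of freedom (11 homes). The ICCs are assumptions. The number of residents who gave self-reports and the number of homes must be confirmed first, because the abstract refers to 6 homes.

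The cost is a few corrected sentences and a few lines of code. The stated figure may become less favourable.

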### Data collection

Processes and outcomes of NTD include data gathered from residents, families, care teams, and the organization (Table 2). Measures for the residents included quality of life, quality of life for people with ADRD, enhanced care experiences, resident centredness and choice and control, satisfaction with NTD*,* and functional and cognitive status indicators (Selected items from the Minimum Data Set –LTC 2.0) (Table 3). Family measures included proxy quality of life indicators, enhanced care experiences, involvement in care and decision making, and satisfaction with NTD. Measures for the team included beliefs and actions, perception of role enactment and team functioning, continuity in assignments, enhanced care experiences, staff-resident relationships and job satisfaction. Organizational descriptors included work distribution, staff turnover and retention. Data were collected through observations, interviews, focus groups, surveys, medical record and chart reviews, and database reviews. Data were collected between March 2013 and March 2017. Data analysis and manuscript writing is ongoing.

**Table 2 Tab2:** Variables and Measurement Schedule

Sample	Category	Variables	Measurement Schedule
Resident	Demographics	Age, gender, marital status, unit	All assessments
	Quality of life indicators	Quality of Life Scales for Nursing Home Residents by Kane	Baseline and every 6 months
	Quality of life for people with ADRD	Observing Quality of Life in Dementia (OQOLD) Measure	baseline and every 6 months
	Resident centredness	CARE Profile	baseline and every 6 months
	Resident’s choice and control	Health-Related Quality of Life Measure	Baseline and every 6 months
	Functional and cognitive status	Depression Rating Scale, Index of Social Engagement, weight, CHESS scale, feeding tube, VAS Pain Scale, pressure ulcers (BWAT), physical restraint use, Activities of Daily Living (ADL Self-Performance Hierarchy Scale), indwelling catheter use, dlirium symptoms (CAM), number of falls, UTIs, new infections, use of anti- psychotics and anti- depressants, number of acute care admissions	Baseline and every 6 months
	Semi-structured interviews	Experiences related to the NTD program implementation	Every 12 months
Staff	Demographics	Position, proportion of time spent with residents, employment status (i.e. full-time, part-time, casual), shift type (i.e. day, evening, night), education, years worked in NH, years worked at current NH

**Table 3 Tab3:** Measurement Tools

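### The stated power of 0.81 is attached to 2112 residents served, not to the 1110 residents in the study sample, and does not follow from its own inputs

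*Protocol article*

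**What the plan says.** All of the relevant figures stand in one paragraph of the Protocol article, Methods, Sample and recruitment.

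- **Origin of 2112:** "Data were available from 11 LTC homes, serving 192 residents, which is approximately 2112 residents in total". This is the number of residents whom the homes serve.
- **Study sample:** "The sample for the study included residents", with n = 1110 in the parenthesis that follows.
- **Test:** the power to detect an increase in residents' "self-reported quality of life was based on a one-sample t-test".
- **Inputs:** "Assuming an effect size of 0.2, standard deviation of 10, and sample size of 2112".
- **Result:** "sample size of 2112, the study will have a power of 0.81 to test change over time".

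The paragraph gives no alpha and no sidedness. It does not say whether 0.2 is standardised or in scale points, or whether the SD refers to the score or to the change. It also says both that no sample size calculation was completed and that such calculations were run in SAS.

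Three other places bear on the point. Table 2 schedules the resident quality-of-life scale at baseline and every 6 months, and lists a separate observed measure for residents with dementia, the "Observing Quality of Life in Dementia (OQOLD) Measure". Ethical considerations says that consent was obtained from participants individually. Objective 3 plans mixed models that account for site differences.

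**The concern.** A power figure describes a particular number of analysable observations. Here that number is everyone served by the homes, although the enrolled sample is reported in the same paragraph and is about half as large. A one-sample t-test of change also needs two self-reports from the same resident, and the paragraph makes no allowance for residents without a second one.

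This is the article's only quantitative statement of what the study can detect. If it stands, any result on quality of life, and a null result in particular, will be read against a power of 0.81 that was not calculated for the study sample and that the stated inputs do not produce.

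**Working it through.** **Inputs from the document:** 11 homes, 192 residents per home, N = 2112 in the power statement, resident sample 1110, effect 0.2, SD 10, one-sample t-test, stated power 0.81.

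**Assumptions, because the document is silent:** two-sided alpha 0.05 (one-sided shown as well), and home-level ICC from 0.01 to 0.10.

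**Step 1: the two sample sizes.** 11 × 192 = 2112, and 1110 / 2112 = 52.6%.

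**Step 2: try to reproduce 0.81 at N = 2112.** Power comes from the noncentral t distribution with n − 1 degrees of freedom and noncentrality d × √n. There are two readings of the effect:

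- raw: 0.2 points with SD 10, so d = 0.2 / 10 = 0.02
- standardised: d = 0.2

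| N | d | d × √N | Power, two-sided | Power, one-sided |
|---|---|---|---|---|
| 2112 | 0.02 | 0.92 | 0.15 | 0.23 |
| 2112 | 0.2 | 9.19 | about 1.00 | about 1.00 |
| 1110 | 0.02 | 0.67 | 0.10 | 0.16 |
| 1110 | 0.2 | 6.66 | >0.99 | >0.99 |

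Neither reading gives 0.81 at 2112, so changing N alone does not repair the statement.

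**Step 3: what would give 0.81?** Two-sided at alpha 0.05, it would need one of the following:

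- about 203 residents with d = 0.2
- about 20,136 residents with d = 0.02
- at N = 2112, a difference of about 0.62 points with SD 10, an effect that the article does not state

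Among the variants tried, values near 0.81 at 2112 appeared only after an unstated input was added. A home-level ICC of 0.05 with d = 0.2 gives 0.80. A within-person correlation of about 0.95 with a raw effect of 0.2 points gives 0.83. The article mentions neither.

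**Step 4: clustering by home, d = 0.2, 11 homes.** Design effect = 1 + (m − 1) × ICC, with m = 1110 / 11 = 100.9, and effective n = 1110 / design effect. For 2112, m = 192. Power is two-sided, with no small-cluster correction.

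| ICC (assumed) | Design effect, N = 1110 | Effective n | Power, N = 1110 | Power, N = 2112 |
|---|---|---|---|---|
| 0.01 | 2.00 | 555 | 0.997 | >0.999 |
| 0.02 | 3.00 | 370 | 0.97 | 0.99 |
| 0.05 | 6.00 | 185 | 0.77 | 0.80 |
| 0.10 | 10.99 | 101 | 0.51 | 0.53 |

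Under the standardised reading, the ICC matters far more than the change from 2112 to 1110. Under the raw reading, power is low whatever the ICC.

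**The case against.** The strongest reply is that this is a reporting matter. The article calls the study pragmatic and says that no formal sample size calculation was done. Data collection ended in March 2017, so the figure changes no estimate, and both 2112 and 1110 are disclosed in the same paragraph. Objective 3 plans mixed models, which can use residents without complete pairs. All of this stands, and it limits the consequence. It does not make 0.81 a correct figure for the sample described.

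A reader might go further and infer that the study is underpowered. The documents do not support that. With a standardised effect of 0.2 and no clustering, power at 1110 is above 0.99, and even 310 residents would give 0.94. A figure such as 0.54 at 1110 arises only by taking 0.81 at 2112 as valid and solving back to the 0.62-point effect of Step 3.

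A reader might also infer that the usable pairs are far fewer than 1110 because of death, discharge or dementia. The article gives no attrition rate and does not say what the 1110 represents. Listing an observed measure for dementia does not show that those residents lack self-reports. The pairs cannot exceed the enrolled residents; how far below they fall is unknown.

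The abstract gives 6 homes rather than 11, and 6 × 192 = 1152. That is a separate discrepancy. It casts doubt on the base of 2112, but this point does not rest on it.

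**Conclusion.** The point holds in two parts, both within one paragraph. First, the power is stated for 2112 residents served, whereas the sample is 1110. This needs no assumption. Second, 0.81 does not follow from the stated effect, SD and N under either reading of the effect, one- or two-sided at the assumed alpha of 0.05: 0.15 to 0.23 if the effect is in points, and about 1.00 if it is standardised.

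The direction of the error cannot be settled from the article. At 1110 residents, two-sided, power is about 0.10 if the effect is raw and above 0.99 if it is standardised and clustering is ignored. With d = 0.2 and 11 homes it runs from 0.997 to 0.51 as the assumed ICC goes from 0.01 to 0.10. The study should not be called underpowered, or adequately powered, until the effect scale and the clustering are stated.

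**What to change.** Withdraw the power of 0.81 at 2112, and keep 2112 only as the number of residents served. Restate power, or the detectable change, on the number of enrolled residents with a baseline and at least one follow-up self-reported quality-of-life score (at most 1110). With it, state:

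- whether the effect of 0.2 is in scale points or standardised
- whether the SD of 10 is that of the score or of the change
- alpha and sidedness
- an allowance for clustering by home, with the ICC used, consistent with the mixed models planned under Objective 3

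In the same edit, reconcile the two statements on whether a sample size calculation was done, and confirm the number of homes.

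The cost is a count in the existing database and one restated figure, which may be less favourable than 0.81. No data collection or analysis changes.
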